# 2.- RATIONALE

## 2.1 Introduction

Non-Hodgkin's Lymphomas (NHLs) are a heterogeneous group of lymphomas with different behaviours and prognoses. Lymphoma originates when healthy B cells, T cells or NK cells from the lymphatic system change and begin to grow without control, which can lead to tumour formation. As lymphatic tissue is present in essentially all parts of the body, NHL may appear in any of them and disseminate, or metastasise, to almost any organ. It often starts in the lymph nodes, liver, spleen or bone marrow. However, it can also affect the stomach, intestines, skin, thyroid gland, brain or any other part of the body^1^.

Depending on their behaviour, they can be divided into two groups: indolent, or slow-growing, lymphomas and aggressive, or fast-growing, lymphomas. The former are difficult to cure if they spread throughout the body and advance slowly (they can even remain unchanged for many years without needing to be treated). The latter, in contrast, can often be cured even though they may be widespread, although they endanger the patient’s life in the short term if not treated early enough. Depending on the lymphocyte concerned, lymphomas are considered to be B-type (the most common), T-type or NK-type, etc.^2^.

This year, it is calculated that 72,240 new cases of NLH will be diagnosed in the USA (40,080 men and 32,160 women). Although some sub-types of NLH are common in children, NHL is more common in adults, with the risk increasing with age. Indeed, around half of patients are aged 66 years or higher. NLH is the seventh most common cancer in both men and women, and this disease represents 4% of all cancers in the USA^1^. According to data from GLOBOCAN 2012 presented by the Spanish Society of Medical Oncology (SEOM), a five-year prevalence of tumours in both sexes of 6285 cases is estimated for Spain in 2017 (general population)^3^.

There are currently different types of treatment for NLH, including chemotherapy, radiotherapy, targeted therapy with newer drugs that block certain functions of the lymphoma cell and immunotherapy.

The incorporation of immunotherapy in malignant haemopathies over the past 10 years has resulted in a favourable change in the therapeutic options available for Non-Hodgkin's Lymphoma (NHL). Rituximab (anti-CD20) has recently become the cornerstone for the treatment of both aggressive and indolent lymphomas.

Rituximab incorporates the first generation of anti-CD20 monoclonal antibodies to be used as biological therapy in B-type lymphoproliferative syndromes, autoimmune diseases and other conditions in which B lymphocytes proliferate. It is a chimeric murine/human monoclonal antibody obtained by genetic engineering comprising a glycosylated immunoglobulin with the constant regions from human immunoglobulin G1 (IgG1) and murine light- and heavy-chain variable region sequences. Rituximab binds specifically to the membrane antigen CD20, a non-glycosylated phosphoprotein located in pre-B and mature B lymphocytes in both normal and malignant cells^4^.

At a dose of 375 mg/m^2^, rituximab has shown its efficacy and low toxicity profile, and is the most widely used drug in mono- or combination therapy for the treatment of various CD20-positive conditions^5-11^. The therapeutic indications currently approved in the summary of product characteristics for NHL include:

Combination with chemotherapy in the treatment of patients with stage III-IV follicular NHL who have not been treated previously.

The maintenance treatment of patients with relapsed or refractory follicular NLH who respond to induction therapy with chemotherapy alone or in combination with rituximab.

As monotherapy in the treatment of patients with stage III-IV follicular NHL resistant to chemotherapy or who are in their first or second relapse.

In combination with CHOP (cyclophosphamide, doxorubicin, vincristine, prednisolone) chemotherapy for the treatment of patients with CD20-positive diffuse large B-cell NHL (DLBCL).

As indicated in the summary of product characteristics, one notable and characteristic side-effect is hypersensitivity reactions (severe dyspnoea, bronchospasm or hypoxia). The causes of this type of reaction are the murine nature of the drug, tumour lysis syndrome and cytokine release syndrome^12^, which occur upon administration. The prevention of such hypersensitivity reactions requires slow administration of the drug. The first administration is the slowest, with an initial infusion rate of 50 mg/h in the first 30 minutes. Subsequently, and in the absence of a reaction, the rate can be increased on steps of 50 mg/h every 30 minutes up to a maximum of 400 mg/h. Subsequent infusions can start at a rate of 100 mg/h, increasing in steps of 100 mg/h every 30 minutes up to a maximum of 400 mg/h. As such, each infusion of rituximab, together with the premedication administered to prevent an infusion-related reaction, can take more than 3 hours, thus representing a significant workload for the day hospital and obliging patients to remain at the hospital for several hours.

To overcome these drawbacks, on 02 June 2017, the FDA approved a new formulation of [rituximab](https://www.cancer.gov/Common/PopUps/popDefinition.aspx?id=CDR0000045525&version=Patient&language=Spanish) in combination with the [enzyme](https://www.cancer.gov/Common/PopUps/popDefinition.aspx?id=CDR0000046081&version=Patient&language=Spanish) hyaluronidase, which allows subcutaneous administration in 5 or 7 minutes instead of intravenous infusion.

The clinical experience with the subcutaneous MabThera formulation in Non-Hodgkin's Lymphoma is based on data from a phase III (SABRINA BO22334), randomised multi-centre non-inferiority clinical trial in untreated patients with follicular lymphoma in which, in addition to investigating the non-inferiority as primary endpoint, the pharmacokinetic profile, efficacy and safety of the subcutaneous MabThera formulation (combination of CHOP or CVP with rituximab SC vs IV) were also investigated, demonstrating the same efficacy and safety thereof^12^.

The approval stipulates that the [subcutaneous](https://www.cancer.gov/Common/PopUps/popDefinition.aspx?id=CDR0000045914&version=Patient&language=Spanish) treatment can only be used after patients have received at least one treatment of IV rituximab with good tolerance due to the risk of hypersensitivity and other serious side-effects during the first infusion^13^. The subcutaneous administration of rituximab has allowed the workload at day hospitals to be reduced and improved patients’ quality of life.

In July 2017, Kern Pharma launched Truxima, the first biosimilar for rituximab. Pharmacokinetics and pharmacodynamics studies comparing Truxima with MabThera showed that the former is very similar from a chemical structure, purity and biological activity viewpoint. In real life, Truxima has been compared with MabThera in various phase I/III clinical trials and has been shown to be not inferior in terms of efficacy, and to have similar effects in terms of tolerability and safety^14-16^.

Currently, given the same efficacy and lower cost, Osakidetza has prioritised use of the biosimilar rather than MabThera. The subcutaneous administration of rituximab has been used at the Araba University Hospital since 2017. Given approval of biosimilar rituximab at a lower price, the possibility of returning to intravenous administration has been evaluated. However, as noted above, intravenous administration requires a longer administration time. This, in turn, leads to a higher workload for the day hospital and a longer stay there for patients.

Since 2010, the Haematology Department at the Araba University Hospital has protocolised that those individuals who tolerate the maximum rate of 400 mg/h at the first infusion will receive the second and subsequent infusions at an initial rate of 400 mg/h. No significant complications have been reported since the start of this protocol. Furthermore, the use of this protocol can shorten the infusion time to approximately two hours.

There have been some attempts to shorten the administration time for intravenous rituximab. In this regard, some studies have reported that the administration of rituximab over 60 minutes is viable and risk-free^16,17^. However, even with this infusion rate, the overall administration time (together with the premedication) would not decrease to less than 2 hours.

In order to reduce the administration regimen and provide a genuine alternative to the administration of subcutaneous rituximab, it has been proposed to perform an ultra-rapid infusion on 30 min.

As noted in the summary of product characteristics, the maximum permitted concentration of rituximab is 4 mg/mL. For a normal individual with a body surface area of 1.8 m^2^ (weight of 70 kg and height of 1.7 m), the total dose of rituximab is 675 mg, therefore dilution in 250 ml of saline would lead to a rituximab concentration of 2.7 mg/ml.

The recommended infusion rate from the second administration onwards (provided the maximum rate of 400 mg/h is achieved in the first infusion) is to start at 100 mg/h and progressively increase this to 400 mg/h. As discussed previously, standard practice at our hospital, in accordance with numerous publications, is direct administration at 400 mg/h from the second infusion onwards. Moreover, the summary of product characteristics allows faster infusions in patients with rheumatoid arthritis, who can receive a faster infusion at the second and subsequent sessions, starting at a rate of 250 mg/hour for the first 30 minutes and then 600 mg/hour for the following 90 minutes. If this faster infusion is tolerated, the same regimen can be used when subsequent infusions are administered.

With the experience at our hospital, we have not observed infusion-related complications with the administration of 400 mg/h, and given the indications in the summary of product characteristics the option to increase the infusion rate further still remains. We believe that an increase in the infusion rate should not have an effect in safety, would reduce the workload at the day hospital and would impact patients’ quality of life by reducing their stay at the hospital.

The aim of this pilot study is therefore to evaluate the safety of an ultra-rapid infusion of Truxima in NHL patients over 30 minutes.

# 3.- AIM AND PURPOSE OF THE STUDY

## 3.1. Hypothesis

Increasing the infusion rate for rituximab is as safe as administration under standard practice (400 mg/h).

## 3.2 Study population

**3.2.1- PRIMARY ENDPOINT**

To evaluate the safety of a rapid, ultrarapid and ultrarapid plus infusion of rituximab based on the percentage of grade 2/3 or higher infusion-related reactions in comparison with the administration of rituximab as per standard clinical practice at the standard rate of 400 mg/h.

Infusion-related reactions are defined as adverse events that occur in the first 24 hours after infusion of rituximab and which are considered to be related to infusion of the drug in the investigator's opinion.

Infusion-related reactions will be graded as the EORTC guidelines: Common Terminology Criteria for Adverse Events (CTCAE) Version 5.0 of EORTC (27 November 2017)

| **GRADE** | **REACTION** |
| --- | --- |
| Grade I: Mild | - - Transitory reaction   - Infusion not suspended   - No indication for intervention |
| Grade II: Moderate | - - Infusion suspended, with rapid recovery of symptoms after symptomatic treatment (e.g., antihistamines, NSAIDs, analgesia, volume support)   - Prophylactic medication for less than 24 hours |
| Grade III: Severe | - - Prolonged symptoms (e.g., slow response to symptomatic medication or suspension of infusion)   - Symptoms recur after initial improvement   - Hospitalisation indicated |
| Grade IV: Very severe | - - Life-threatening symptoms   - Urgent intervention indicated |
| Grade V: | - - Related death |

**3.2.2- SECONDARY ENDPOINTS**

- Determine the intensity of the infusion-related reactions between rapid, ultrarapid and ultrarapid plus infusions of rituximab.
- Determine the time until the infusion-related reaction.

# 4.- TRIAL DESIGN

**4.1.- Variables**

Primary variable:

-Percentage of grade 2/3 or higher infusion-related reactions for the rapid, ultrarapid and ultrarapid plus infusions in comparison with the administration of rituximab as per standard clinical practice at the standard rate of 400 mg/h.

** Infusion-related reactions are defined as adverse events that occur in the first 24 hours after infusion of rituximab and which are considered to be related to infusion of the drug in the investigator's opinion.*

Secondary variables:

- Grade of infusion-related reactions (1-5 as per CTCAE version 4.0) occurring in each study group.

- Time (in minutes) between the start of infusion and onset of the infusion-related reaction.

Other variables:

- Age (years)

- Sex (male/female)

- Infusion group (rapid, ultrarapid or ultrarapid plus)

- Treatment type (induction/maintenance)

- Therapy type (rituximab in monotherapy/combination therapy - specify the type of concomitant treatment: chemotherapy, radiotherapy, targeted therapy, etc.)

- Lymphoma type (specify diagnosis)

- Rituximab cycle number

- Blood pressure, temperature, oxygen saturation and heart rate before starting and after finishing rituximab infusion

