# 6.- SUBJECT TREATMENT

When the patient attends the haematology surgery and has tolerated the maximum intravenous administration rate for rituximab (400 mg/h) during the first or second infusion, they will be invited to participate in the study and will be given the informed consent. If the patient complies with all the inclusion criteria and none of the exclusion criteria, and decides to participate, they will be given an appointment to attend the day hospital for administration of their treatment cycle at the infusion rate being studied at that time.

Three successive intervention groups with different infusion rates (rapid, ultrarapid and ultrarapid plus) will be established. The procedure for each cohort will be considered to be safe if fewer than four mild to moderate infusion-related reactions occur in the 16 patients from the corresponding cohort (25% of reactions). The onset of one or more grade 2 or higher infusion-related reactions will imply that the cohort is not safe and the clinical trial will be suspended. Before commencing the next cohort, a haematology specialist not linked to Araba University Hospital Haematology Department will carry out a safety monitoring. This will involve an evaluation of all infusions performed, with access to the progress reports (medical and nursing) to determine whether a reaction has occurred and the grade thereof. In an attempt to minimise the influence of the investigator on the safety evaluation, the safety monitor will receive the progress reports after references to the grade of the infusion-related reaction contained in the electronic medical records have been censored.

Rituximab will be diluted in 250 mL provided the maximum concentration established in the summary of product characteristics (max. 4 mg/mL) is not exceeded. The rituximab dose will not be changed.

If the patient is receiving concomitant chemotherapy, this will be administered after rituximab once the absence of adverse reactions has been confirmed.

The interventions applied in each of the three study groups are described below:

RAPID INFUSION GROUP

Administration of the IV premedication half an hour prior to the infusion of rituximab as per the standard regimen; generally, dexchlorpheniramine 5 mg IV and paracetamol 1 g IV half an hour prior to rituximab.

The rituximab dose will then be administered at the standard dose: 375 mg/m^2^ diluted in 250 mL of saline over one hour, as follows:

- - - First 10 minutes at 450 mg/hour

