    - Subsequent 50 minutes at 720 mg/hour

A total of 16 infusions will be included in this group and the safety thereof will be evaluated. If the number of AEs is not higher than normal (more than three infusion-related reactions), the second intervention will commence. In the event that the number of infusion-related reactions is higher than in standard clinical practice, the study will be suspended without continuing with the following groups.

ULTRARAPID INFUSION GROUP

Administration of the IV premedication half an hour prior to the infusion of rituximab as per the standard regimen; generally, dexchlorpheniramine 5 mg IV and paracetamol 1 g IV half an hour prior to rituximab.

The rituximab dose will then be administered at the standard dose: 375 mg/m^2^ diluted in 250 mL of saline over half an hour, as follows:

- - - First 10 minutes at 450 mg/hour.
    - Subsequent 20 minutes at 1800 mg/hour.

A total of 16 infusions will be included in this group and the safety thereof will be evaluated. If the number of infusion-related reactions is not higher than normal (more than three infusion-related reactions), the third intervention will commence. In the event that the number of infusion-related reactions is higher than in standard clinical practice, the study will be suspended without continuing with the following group.

ULTRARAPID PLUS INFUSION GROUP

Administration of the oral premedication half an hour prior to the infusion of rituximab as per the standard regimen for administration of subcutaneous rituximab: dexchlorpheniramine 4 mg orally and paracetamol 1 g orally half an hour prior to rituximab.

The rituximab dose will then be administered at the standard dose: 375 mg/m^2^ diluted in 250 mL of saline over half an hour, as follows:

- - - First 10 minutes at 450 mg/hour.
    - Subsequent 20 minutes at 1800 mg/hour.

A total of 16 infusions will be included in this group and the safety thereof will be evaluated. This ultrarapid infusion regimen will be considered to be safe if the number of infusion-related reactions is three or less.

Safety will be evaluated by monitoring infusion-related reactions, including all haematological and non-haematological serious and non-serious adverse events related to the study drugs. If an infusion-related reaction occurs, the standard administration rate of 400 mg/h will be used.

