# 8.- STATISTICS

## 8.1.- Sample Size

The expected number of infusions is 48, distributed into 16 infusions per group. It is recommended to include between 30 and 50 measurements in a pilot study^18,19^.

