## 8.2.- Statistical analysis

A general description of all study variables will be performed. Qualitative variables will be expressed as absolute frequencies and percentages, and quantitative variables as the mean and standard deviation (median and 25th and 75th percentiles if they do not follow a normal distribution). The primary endpoint will be evaluated using a chi-squared test (with a Fisher correction if it does not comply with the criteria) and the secondary endpoints will be evaluated by performing a chi-squared test (with a Fisher correction if they do not comply with the criteria) for categorical variables, and Student’s t-test (or Mann–Whitney U-test if they do not follow a normal distribution) will be applied for continuous variables. A Kaplan Meier survival analysis will be applied to determine the time to the infusion-related reaction. A statistical significance level of p<0.05 will be used in all tests. Statistical analysis will be performed using the statistical software packages R (version 3.5.0) and SPSS (version 23.0).

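### The primary test compares with rituximab at 400 mg/h, but the protocol names no 400 mg/h data, so it cannot be run as written; the label of normal for up to 3 of 16 reactions has no source

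*Protocol*

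**What the plan says.** The hypothesis in Section 3.1 is comparative: "Increasing the infusion rate for rituximab is as safe as administration under standard practice (400 mg/h". The primary endpoint (3.2.1), primary variable (4.1) and study description (4.2) repeat the comparison; in 4.1 the percentage of grade 2/3 or higher reactions is taken "in comparison with the administration of rituximab as per standard clinical practice at the standard rate of 400 mg/h". Section 8.2 states: "The primary endpoint will be evaluated using a chi-squared test (with a Fisher correction if it does not comply with the criteria".

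The groups are set in Section 6: "Three successive intervention groups with different infusion rates (rapid, ultrarapid and ultrarapid plus) will be established". Section 8.1 allots the sample: "The expected number of infusions is 48, distributed into 16 infusions per group". The group variable in 4.1 has three levels: "Infusion group (rapid, ultrarapid or ultrarapid plus".

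Section 6 has two safety rules. A cohort is safe with fewer than four mild to moderate reactions among 16, and a single grade 2 or higher reaction makes it unsafe and suspends the trial. For the rapid group the count rule is worded: "If the number of AEs is not higher than normal (more than three infusion-related reactions), the second intervention will commence". The sentence after it describes the opposite outcome as more reactions than in standard clinical practice.

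On experience at 400 mg/h, Section 2.1 says: "we have not observed infusion-related complications with the administration of 400 mg/h". Elsewhere it says, more narrowly, that no significant complications have been reported since the department's protocol began in 2010. Neither statement gives a numerator or denominator.

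**The concern.** A chi-squared or Fisher test needs counts from at least two groups. Here one side of the comparison has no data. In the trial procedures, 400 mg/h appears only as an eligibility condition (Sections 5 and 6) and as the rate used after a reaction (Section 6). Neither is a comparator.

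An analyst would have to test the three fast cohorts against each other, or choose a 400 mg/h reference after the results are known. The first does not address the hypothesis. The second leaves the primary p-value open to a choice made after the fact.

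The unsourced label in Section 6 adds to this. A cohort could be reported as no worse than standard practice when the protocol never says what rate standard practice has.

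**Working it through.** **1. The protocol's own figures.** 3 cohorts × 16 infusions = 48, as in Section 8.1. 4/16 = 25%, as in Sections 5 and 6. Both reproduce. Infusions left for a 400 mg/h group: 48 − 48 = 0.

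**2. Testing the cohorts against each other.** The primary variable counts grade 2 or higher reactions. Section 6 tolerates none, so every cohort that passes has 0/16 primary events, and passing cohorts give a table with no events. If a full cohort of 16 had one such reaction against 0/16 in an earlier cohort, two-sided Fisher p = 1.0.

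**3. Dependence on an unnamed control.** The protocol gives no control size, so assume 0 reactions in N infusions at 400 mg/h. Two-sided Fisher p:

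| N | 1/16 vs 0/N | 3/16 vs 0/N |
|---|---|---|
| 16 | 1.0 | 0.226 |
| 50 | 0.242 | 0.012 |
| 100 | 0.138 | 0.0022 |
| 200 | 0.074 | 0.0003 |

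At N = 500, 1/16 gives p = 0.031. The same trial result is or is not significant at 0.05 depending on a number the protocol does not contain.

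**4. What the label of normal implies.** If more than 3 of 16 is higher than normal, then 3/16 = 18.75% is not. At a true rate of 18.75%, the chance of seeing no reaction is (1 − 0.1875)^16 = 3.6% in 16 infusions and (1 − 0.1875)^48, below 0.01%, in 48. So none observed over years of use would not fit a background at that ceiling, provided the same events were counted. Any cohort that passes can have only grade 1 reactions in this count, so it does not measure the grade 2 or higher primary variable.

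**5. What the rules let through.** Let p be the true any-grade rate per infusion and f the share of reactions that are grade 2 or higher. The protocol gives neither; both are assumed, with independent infusions.

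P(pass both rules) = Σ (k = 0 to 3) C(16,k) · [p(1 − f)]^k · (1 − p)^(16−k)

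With f = 0 this is the count rule alone.

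| p | f = 0 | f = 10% | f = 20% | f = 30% |
|---|---|---|---|---|
| 15% | 0.79 | 0.65 | 0.54 | 0.44 |
| 20% | 0.60 | 0.48 | 0.38 | 0.29 |

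At f = 0, a true rate of 5% passes with probability 0.993 and 10% with 0.932.

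**6. What can be reported without a comparator.** Exact (Clopper–Pearson) two-sided 95% intervals: 0/16 gives 0 to 1 − 0.025^(1/16) = 20.6%; 3/16 gives 4.0 to 45.6%.

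**The case against.** The strongest defence is that this is a declared pilot. Section 4.5 says the sample is too small to show differences from standard treatment and that assignment is not random. Escalation, suspension and the safety verdict follow the count rules and an independent haematologist's review, not a p-value. This stands as a limit on the harm. It does not supply the comparator: Section 4.5 concedes low power, not absent data on one side. An unseen analysis plan might specify a historical control, but nothing in the protocol points to one, and which control data are collected is a matter of design.

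Three stronger readings are tempting and not supported.

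- A reader might infer that 3 of 16 flatly contradicts the hospital's experience. The tension with the unqualified statement in Section 2.1 is real; with the statement about significant complications it is weaker. Grade 1 reactions need no intervention or suspension of the infusion, and the hospital may never have counted them as complications. Section 6 also states the count elsewhere as a tolerance for calling a cohort safe, not as a background estimate. For the primary variable itself the tolerated number is zero, which agrees with Section 2.1.
- A reader might infer that patients' own earlier 400 mg/h infusions are ruled out because eligibility selects on tolerance. Section 5 selects on the first or second infusion only. Later infusions at that rate, for example in maintenance patients, are not directly selected by it. They are simply not named as data.
- A reader might take 0.79 and 0.60 as the chance that an unsafe regimen passes, or express them as multiples of a background rate. They hold only if every reaction is grade 1, and the protocol gives no background rate to form a multiple from.

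**Conclusion.** The primary comparison with 400 mg/h cannot be carried out from the groups and data the protocol defines. This needs no assumption: three cohorts, 48 infusions and three group levels, none at 400 mg/h, and no external reference named. A between-cohort test is no substitute, because passing cohorts have no primary events.

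Secondarily, the description of up to 18.75% as normal or as standard practice is unsourced, concerns a different event from the primary variable, and sits uneasily with Section 2.1 without clearly contradicting it. The pass probabilities of 0.79–0.44 at a true rate of 15% and 0.60–0.29 at 20% rest on an assumed grade 2 or higher share of 0 to 30%.

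This should be fixed before the first cohort opens. It is not graver than that, because decisions during the trial rest on the count rules and the external monitor.

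**What to change.** In Sections 3.1, 3.2.1, 4.1, 4.2 and 8.2, choose one option.

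- **(a) Drop the comparison.** Remove the comparison with 400 mg/h and its chi-squared/Fisher test. Report each cohort's grade 2 or higher and any-grade proportions with exact confidence intervals. This is a change of wording only, and it suits a pilot of 16 infusions per cohort.
- **(b) Name the comparator before the first cohort opens.** Define a 400 mg/h dataset with its number of infusions, rate, eligibility, grading and 24-hour window, and write these into the protocol. The department's records since 2010 are a possible source. The cost is a limited chart review, and retrospective records may miss mild reactions.

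With either option, give a source for the labels of normal and standard clinical practice in Section 6 or remove them, and reconcile them with Section 2.1 and with the two safety rules in Section 6. This point does not ask for a different threshold.
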